## Abbreviations

Empathica: Expectation Management for Patients in Primary Care. [the name of the overarching project]

EMPathicO: Empathy and Conveying Optimism. [the name of the digital training intervention that we have developed and are trialling]

GP: General Practitioner

HOOS: Hip and Disability Osteoarthritis Score

KOOS: Knee Injury and Osteoarthritis Score

MISS: Medical Interview Satisfaction Scale

NICE: National Institute for Health and Care Excellence

NRS: Numerical Rating Scale

OA: Osteoarthritis

PCP: Primary Care Practitioner, e.g., GP, physiotherapist, nurse

PEI: Patient Enablement Index

TEX-Q: Treatment Expectation Questionnaire

TSC: Trial Steering Committee

## Plain English Summary

Osteoarthritis pain is common, costly, and challenging to manage in busy primary care settings. While various drug-based and non-drug-based treatments are recommended, patients still experience pain, poor quality-of-life, and drug side effects. Regardless of which treatment patients receive, excellent practitioner-patient communication can significantly reduce patients' pain while improving quality of life and satisfaction with care. Patients experience less pain after consulting practitioners who show empathy and encourage optimism about treatment. Yet practitioners vary widely in how much they show empathy, use a positive approach, and/or use key non-verbal skills. A simple intervention concentrating on improving key elements of empathy and non-verbal communication is likely to be effective and efficient. We have developed an online training package for primary care practitioners (including General Practitioners - GPs, physiotherapists, and nurses) to enhance their consultation skills to show more empathy, improve their non-verbal communication skills, and encourage patients with osteoarthritis to have positive yet realistic expectations. This training package is called EMPathicO. Ultimately, we aim for our training package to enable practitioners to improve the long-term effectiveness of all drug and non-drug therapies for osteoarthritis pain, reduce patients' pain and improve quality of life.

We plan to conduct a small 'feasibility' trial to help us design a large, fundable, clinical trial to test the online empathy training package against usual GP care.

Our aims for the feasibility trial are to assess a range of ways to recruit practices and their patients to participate in a trial and what approaches are most effective and acceptable. We will also assess ways to consent patients, the practicalities and acceptability video record consultations, ways to collect our proposed outcome measures and assess GP use and experience of the online training tool. We will involve patient representatives in the design of the feasibility study to help ensure proposed procedures are relevant and realistic.

**Methods.** This feasibility trial will be undertaken in a diverse range of general practices in the South of England and will involve approximately 10 GP practices, 20 primary care practitioners, and up to 280 patients. Practices will be randomised, and practitioners in 5 of the GP practices will undertake the EMPathicO online training and those in the other 5 GP practices will continue normal practice. Those who continue normal practice will have access to the training after the feasibility study is completed. Data collected for the feasibility study will include: video recordings of consultations with patients, patient-reported questionnaires, and practitioner-completed questionnaires. with osteoarthritis to form a baseline and a resource to use during the training. Patient-reported questionnaires ask them about their symptoms, quality of life, satisfaction and ability to cope with their illness. Practitioners and practice staff will be asked to participate in focus groups and/or telephone interviews. Patients will be asked to participate in telephone interviews. The focus groups and interviews will explore how participants found the feasibility study procedures and the online training.

**Results.** We will collect information on all the feasibility trial procedures to inform the design of a large trial to test the clinical and cost effectiveness of the online training

## Expert Summary

Osteoarthritis (OA) pain is prevalent, personally and economically costly, and challenging to manage in busy primary care settings. Pharmacological and non-pharmacological treatments are recommended but patients report adverse effects and limited benefits. Regardless of which treatment patients receive, excellent practitioner-patient communication can significantly improve pain, quality of life, and satisfaction. Previous work suggests that people in pain have better outcomes when practitioners communicate empathically and encourage realistic and positive expectations about treatment. However, this evidence remains to be implemented in practice in a pragmatic format that engages practitioners effectively, and practitioners vary widely in how much they express empathy to their patients. We have addressed this by developing a digital intervention to enhance primary care practitioners' skills in the context of managing OA pain, focusing on empathic communication and expectation management. This training package is called EMPathicO. Furthermore, we anticipate that these skills are also relevant to patients consulting for other conditions. This feasibility study is designed to see how best to evaluate our intervention in an eventual cluster randomised controlled trial in primary care. Our aims and associated objectives are:

- 1) to establish methods to maximise recruitment and minimise attrition, in practices with a range of socio-demographic areas (barriers and enablers)
  - a. to assess recruitment rates associated with different methods of recruitment
  - b. to assess retention rates
  - c. to identify barriers to recruitment of practices, PCPs, and patients, and ways to overcome them
  - d. to identify enablers of recruitment of practices, PCPs, and patients, and ways to harness them
  - e. to identify barriers to retention of practices, PCPs, and patients, and ways to overcome them
  - f. to identify enablers of retention of practices, PCPs, and patients, and ways to harness them
- 2) to identify feasible randomisation and consent procedures and finalise inclusion/exclusion criteria
  - a. to test the feasibility of cluster randomisation.
  - b. to test the feasibility of different ways of taking practitioner and patient consent, as outlined below.
- 3) to finalise outcome and process measures
  - a. to test the practical and ethical feasibility of video-recording consultations
  - b. to explore the relevance, feasibility and acceptability of potential outcome measures
  - c. to explore the relevance, feasibility and acceptability of potential process measures
  - d. to explore options for outcome and process measures for all-consulters and OA consultations
  - e. to explore feasible methods of analysing filmed consultations
  - f. to establish likely effect sizes
  - g. to explore data for indicative changes in outcome and process measures
  - h. to explore effective engagement with EMPathicO

To achieve these aims, we will conduct a cluster-randomised feasibility trial in 10 primary care practices (20 practitioners, 80 patients with osteoarthritis, and up to 200 patients attending primary care for other conditions) in the Wessex area. Practices will be randomised (1:1) to our new digital training package or to usual care control. We will explore different ways of recruiting and consenting patients. Patients will complete patient-reported outcome and process measures. Practitioners will complete additional process measures. We will collect extensive data on

intervention usage, recruitment and retention rates, and will explore the recording and analysis of consultations. We will conduct semi-structured qualitative telephone interviews with practitioners, practice staff, and patients. The data will be analysed and interpreted to further improve the intervention, refine our planned trial design including procedures, outcome measures, and sample size. We will consider a full trial feasible and apply for funding if: we achieve 70% of our intended recruitment (14 PCPs, 42 OA patients); if we achieve 50% recruitment we will modify methods; if we achieve under 50% we will investigate reasons to see whether it can be addressed in a full trial. AND 2. 70% of recruited GPs log onto the EMPathicO intervention on LifeGuide; if 50% log on we will modify our incentive and/or reminder plan during the feasibility study.

## Background

### Introduction

In the UK, one third of adults over 45 have sought treatment for osteoarthritis (OA), primarily through general practice, and in 2010 OA was the 11th leading cause of disability. Disability due to OA increased substantially from 1990 to 2010 and will continue increasing with an aging population. NICE Guidelines recommend a patient-centred approach to OA including information and self-management, non-pharmacological interventions (e.g. exercise, manual therapy, aids and devices), and pharmacological management (paracetamol, NSAIDs, corticosteroids, capsaicin, opioids), before considering referral for joint surgery. Non-invasive interventions typically demonstrate only small to moderate effects. Opioids and intra-articular corticosteroids may have larger short-term benefits but patients are concerned about adverse effects and many patients discontinue their use after a few weeks. While these treatments can help patients, their full potential is often not realised. Although practitioners typically perceive musculoskeletal pain to be well-managed, patients report ongoing pain and disability.

Regardless of which therapy a patient receives, excellent practitioner-patient communication has the potential to significantly improve patients' symptoms, quality of life, adherence to and satisfaction with care, producing modest benefits that are comparable to many pharmaceutical interventions. Furthermore, sub-optimal consultations represent missed opportunities for benefit and can even be harmful, causing: worse quality of life and symptom management, unwanted prescriptions and non-adherence; unnecessary economic costs; deviation from guideline-recommended treatment; and increased complaints and litigation. Despite communication skills being essential in medical and allied health professional training, patients still report dissatisfaction with practitioner-patient communication. Our recent systematic review showed that the extent to which PCPs express empathy is typically low and varies widely. Fortunately, PCPs are willing to engage in training and even very brief interventions can successfully improve communication skills, including interventions concentrating on non-verbal skills which take no additional time in the consultation and so are likely to be very efficient. However, few interventions have been tested clinically for effects on patients' health, few have been sufficiently well described to allow implementation, and (where details are available) most interventions are prohibitively complex, expensive, and time-consuming, which makes engagement and uptake in the current climate in primary care extremely unlikely. Our research addresses these key limitations.

### Empathico: Enhancing care through empathy and optimism

We are currently finalising a new brief digital training package for PCPs, called EMPathicO. This training package is designed for PCPs to enhance their communication of empathy and optimism through verbal and non-verbal behaviours. Our decision to focus on these aspects was influenced by a recent systematic review conducted by team members demonstrating the potential benefits of communicating empathy and positive expectations and prior work demonstrating the importance of non-verbal communication in primary care.

Training practitioners to enhance their communication of empathy and optimism through verbal and non-verbal behaviours could enhance care for diverse conditions. Indeed, much of the evidence that underpins the importance of these behaviours for patient outcomes, and that we have drawn on to develop EMPathicO, is derived from studies of various conditions including but not limited to osteoarthritis pain. However, interventions targeted to specific audiences and conditions are likely to be more relevant (to recipients) and possibly more effective, particularly if they are also tailored to individuals. Therefore, in developing EMPathicO we aimed to produce a training package that

not only has the potential to be broadly applicable to primary care consultations but also includes the necessary content to allow PCPs to tailor their new skills for use in OA consultations.

To develop EMPathicO we used the systematic multi-component person-based approach (PBA) to put intervention users and beneficiaries at the heart of the design and development process. We integrated evidence-based and theory-based approaches to ground our training package in relevant evidence and theory. We used the BCW (Behaviour Change Wheel) and COM-B (Capability, Opportunity, Motivation model of Behaviour) as our comprehensive theoretical framework to guide intervention design and complement the PBA's focus on intervention users' perspectives.

The work that informed the development of EMPathicO is currently being concluded and written up for publication and includes:

- two literature reviews analysing the components of tested interventions included in a recent systematic review related to communicating empathy (7 interventions) and positive expectations (22 interventions), plus components analysis of a further 35 interventions on empathy;
- a major meta-ethnography synthesizing evidence from 21 studies on patients' and 12 studies on PCPs' perspectives on primary care consultations for OA;
- a behavioural analysis of the communication of empathy and positive expectations;
- a qualitative interview study of 20 PCPs' views about digital training in empathic and optimistic communication in general and for patients with OA in particular;
- two qualitative interview studies of patients' views about doctors' communication for OA (using enacted consultations and written vignettes as stimuli for discussion; ongoing).

Findings from this extensive body of development work were used to draft guiding principles and a logic model that were in turn used to guide the development of an initial draft of EMPathicO. We are currently conducting two further 'think aloud' studies with PCPs (n=20) to iteratively refine the training package based on our analysis of PCPs' experiences and perspectives, with reference to the guiding principles and logic model.

## Aims and Objectives

This feasibility study is needed to establish parameters and methods for a subsequent definitive trial. Following NIHR guidance on pilot/feasibility studies, the aims and associated objectives are:

- 1) to establish methods to maximise recruitment and minimise attrition, in practices with a range of socio-demographic areas (barriers and enablers)
  - a. to assess recruitment rates associated with different methods of recruitment
  - b. to assess retention rates
  - c. to identify barriers to recruitment of practices, PCPs, and patients, and ways to overcome them
  - d. to identify enablers of recruitment of practices, PCPs, and patients, and ways to harness them
  - e. to identify barriers to retention of practices, PCPs, and patients, and ways to overcome them
  - f. to identify enablers of retention of practices, PCPs, and patients, and ways to harness them
- 2) to identify feasible randomisation and consent procedures and finalise inclusion/exclusion criteria
  - a. to test the feasibility of cluster randomisation.

- b. to test the feasibility of different ways of taking practitioner and patient consent, as outlined below.
- 3) to finalise outcome and process measures
  - a. to test the practical and ethical feasibility of video-recording consultations
  - b. to explore the relevance, feasibility and acceptability of potential outcome measures
  - c. to explore the relevance, feasibility and acceptability of potential process measures
  - d. to explore options for outcome and process measures for OA consultations and others
  - e. to explore feasible methods of analysing filmed consultations
  - f. to establish likely effect sizes
  - g. to explore data for indicative changes in outcome and process measures
  - h. to explore effective engagement with EMPathicO.

## Methods

### Design

Mixed methods feasibility trial in primary care, designed to evaluate methods for a cluster-randomised trial of EMPathicO in all-consulters with a pre-planned sub-sample of patients with hip and/or knee OA. Henceforth, the participants who are not consulting with hip and/or knee OA are referred to as 'others'. The activities to be undertaken by practices and practitioners, and patients, are summarised in Figure 1 and Figure 2 respectively. The timings are subject to change during the feasibility trial depending on recruitment rates: for example, if necessary, we will extend the time available for recruiting patients.

**Figure 1: Practice and Practitioner Activities**

[figure not shown]

[figure not shown]

Note. \* Patients whose consultations are filmed pre-randomisation are not otherwise included in the feasibility trial.

**Figure 2: Patient Activities (Post-Randomisation)**

[figure not shown]

As Figure 1 shows, both the control group and the EMPathicO group are being asked to film some consultations at two time-points, before and while enrolling patients in the trial. One could argue that the control group should not be filming any consultations, as filming and reviewing one's consultations is a key, and we believe active, component of EMPathicO. However, we anticipate that any future definitive trial will be more likely to attract funding and more likely to influence practice if we can demonstrate that the content of the training is effective above and beyond any non-specific effects of filming and reviewing one's consultations. While this means that the control group does not constitute usual care, it may approximate usual care for newly qualified GPs who are encouraged to practice reflectively and for whom consultation training has been highlighted as particularly important.

In the KEPe-Warm trial, GPs had 1 to 3 weeks to practice implementing their new skills before data collection commenced. We have retained this by allowing 3 weeks for PCPs to undertake the training and practice implementing it in practice before commencing patient recruitment.

## Participants

Participants will be PCPs (primary care providers e.g. GP, physiotherapist, or practice nurse) who see people with OA in primary care on a regular basis and their patients.

## Inclusion/Exclusion Criteria

### Practices:

Inclusion criteria: Primary care practices within Wessex CRN.

Exclusion criteria: Participated in Empathica Development studies 2 or 4 (think aloud studies), as these involve looking at prototypes of the intervention. If they were to be included in this feasibility trial they could contaminate the control arm.

### Practitioners:

Inclusion criteria: primary care provider (e.g. GP, physiotherapist, or practice nurse) seeing people with OA on a regular basis. While we expect most if not all practitioner-participants to be GPs, we want to try to recruit first-contact primary care physiotherapists and practice nurses too because these practitioners (particularly physiotherapists) will be increasingly involved in managing patients with OA in primary care in the future.

Exclusion criteria: none.

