### Randomization.

Cluster randomisation at the practice level, 1:1 ratio, randomising 5 practices to intervention and 5 to control. Randomizing individual PCPs would risk cross-contamination within practices.

In the full trial, we intend to stratify by practice size and location (urban/rural). However, this is not necessary in a feasibility trial (as we are not assessing intervention effectiveness) and is not particularly useful when only randomising 10 practices. Blocked randomisation will be used, with random block sizes of 4 and 6. This will be implemented by means of an Excel file, programmed by our statistician ([name]).

Randomization will be done after PCPs have successfully recorded five baseline consultations (including at least one consultation regarding hip and/or knee OA). When the researchers have confirmed that all participating PCPs in a practice have successfully recorded their baseline consultations, the research team will enter the practice into a cell in the Excel file which will then randomly allocate and display the trial group.

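### Prior exposure to the EMPathicO prototype is screened by practice only, so a think-aloud participant now working at another practice stays eligible and could be allocated to control

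*Protocol*

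**What the plan says.** Under Inclusion/Exclusion Criteria, Practices, the protocol excludes a practice that "Participated in Empathica Development studies 2 or 4 (think aloud studies), as these involve looking at prototypes of the intervention". The reason follows: "If they were to be included in this feasibility trial they could contaminate the control arm".

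The Background section on EMPathicO shows who saw the prototypes: "We are currently conducting two further 'think aloud' studies with PCPs (n=20) to iteratively refine the training package". The participants are described as PCPs, not as practices.

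Under Inclusion/Exclusion Criteria, Practitioners, the entry is "Exclusion criteria: none".

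The Randomization section allocates whole practices, five to each arm, because "Randomizing individual PCPs would risk cross-contamination within practices". Allocation follows baseline filming, so PCPs consent before their arm is known. The Control Group section asks control PCPs to carry on as usual and not to watch their films until the trial ends, when they are given the training.

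**The concern.** The protocol names a specific hazard, a control-arm practitioner who has already seen the training, but applies the rule to the practice. What a PCP learned in a think-aloud session stays with that PCP on a move to another practice or when working at a second one. The practice rule therefore stands in for the exposure it is meant to exclude, and the practitioner criteria expressly add nothing to it.

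Control PCPs who already know the material would bring the arms closer together on patient-rated empathy, enablement and filmed behaviour. That matters for objective 3f (likely effect sizes), objective 3g (indicative changes) and the film comparison, which looks at similarity between arms at baseline and change within arms. An exposed PCP in either arm would also have baseline films that do not show untrained practice. Finalising the eligibility criteria is itself one of the trial's aims, so any gap in them could pass into the full trial.

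**Working it through.** No figure in the protocol depends on this rule, so there is nothing to reproduce. The check has two parts: whether the text leaves the route open, and how large the effect could be.

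**Is the route open?**

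1. Practices: taking part in studies 2 or 4 excludes the practice. This removes every PCP who can enter only through that practice, exposed or not.
2. Practitioners: no exclusions. A PCP entering through a practice that is not barred is eligible whatever they did before.
3. Recruitment and Consent Procedures, Practitioners: describes information, the set-up meeting, equipment and two ways of taking consent. It does not mention a question on earlier participation.
4. Confirming Eligibility (CRF): covers patients only.
5. Control Group and Filming Consultations Procedures: ask control PCPs not to view their films. This cannot undo earlier exposure.

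The route stays open for a think-aloud participant who has changed practice, who also works elsewhere, or whose practice was not counted as having taken part. I take the two think-aloud studies in the Background to be development studies 2 and 4. The shared label supports this, but the protocol does not state it outright.

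**How large could it be?**

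Inputs from the protocol: up to 20 PCPs; up to 60 OA patients (3 per PCP) and up to 120 others (6 per PCP); 0.25 SD as the effect size cited for the full trial, used here only as a yardstick. Assumptions: PCPs split evenly between arms, and each recruits the same number of patients.

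- Control PCPs: 20 / 2 = 10.
- Patients per PCP: (60 + 120) / 20 = 9, so 90 per arm.
- One exposed control PCP: 9 / 90 = 10% of the control arm.

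With k exposed PCPs among m control PCPs, each carrying a fraction c of the full effect, the expected contrast is 0.25 × (1 − c × k / m).

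| Exposed control PCPs (of 10) | c = 0.5 | c = 1 |
|---|---|---|
| 1 | 0.25 × 0.95 = 0.2375 | 0.25 × 0.90 = 0.225 |
| 2 | 0.25 × 0.90 = 0.225 | 0.25 × 0.80 = 0.20 |

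The protocol gives no value for c or k. If only 14 PCPs were recruited (the 70% threshold), there would be 7 in control. One exposed PCP would then be 1/7 = 14%, and at c = 1 the contrast would be 0.25 × 6/7 = 0.214.

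For scale, the standard error of a standardised difference with 90 patients per arm, ignoring clustering, is √(2/90) = 0.149. One fully exposed PCP shifts the contrast by 0.025, and 0.025 / 0.149 = 0.17, about a sixth of a standard error. Clustering would make the standard error larger and that ratio smaller.

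**The case against.** The best defence is that PCPs enter only through practices. The practice rule therefore already removes anyone still working solely at a think-aloud practice, together with unexposed colleagues, and the practitioner entry means only that nothing is added to that filter. The think-aloud studies were still running when the protocol was written, so there was little time to change practice. The same team meets interested practices and might recognise about 20 earlier participants. Looking at a prototype under revision is also weaker than the full training, which includes reviewing one's own films, so complete contamination is the extreme case. All of this stands, and it limits both how likely and how large the problem is. It does not close the route: chance recognition is not an eligibility rule, and an exposed PCP at another practice is eligible as the text is written.

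A reader might infer that the full trial would be undersized or would need many more patients. The protocol does not support this. Planned Analysis takes 0.25 from systematic reviews and refines the calculation with completion rates, ICCs and standard deviations, so the observed contrast is not an input.

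A reader might also infer that PCPs working at two participating practices should be barred. The protocol is silent on such PCPs and does not say that any exist, including among the physiotherapists it hopes to recruit. A blanket bar would exclude PCPs whose practices fall in the same arm, where nothing crosses over. Because practices are staggered, a PCP who consents early may not know which others will join.

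**Conclusion.** The point holds as a minor gap in eligibility. The protocol identifies prototype exposure as a threat to the control arm, screens for it by practice, and leaves the individual PCP unscreened. It would be too strong to say that the practice rule fails: it should catch most exposed PCPs, and those it misses may number zero.

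At full recruitment with an even split, each exposed control PCP dilutes the arm contrast by at most about 10%, and by about 5% if exposure carried half the effect. Both figures assume equal patient numbers per PCP. The reach is limited to objectives 3f and 3g and the filmed-behaviour comparison, all exploratory in a trial that says it does not assess effectiveness. The progression criteria rest on recruitment and LifeGuide log-on, with a completion target for patient-reported outcomes, so this bias in the arm contrast does not enter them.

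**What to change.** Under Inclusion/Exclusion Criteria, Practitioners, replace the present entry with an exclusion such as: personally took part in Empathica development studies 2 or 4, or has otherwise used EMPathicO. Keep the practice-level exclusion.

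Check it at PCP consent, before baseline filming, with one yes/no question on both the in-person and the online form, or against the team's own list of think-aloud participants. Because randomisation comes after baseline filming, any exclusion is then made before allocation and cannot unbalance the arms.

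The cost is one question or one list check. The downside is that a few PCPs may become ineligible, which counts slightly against a target of 20. No rule on working at more than one participating practice is needed for this fix.
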